**1. Study design**

[figure not shown]

**1.1 Rapid appraisal**

6 village schools in Zhangjia have been identified, based on willingness of villagers to participate and ease of transporting stool samples to a local makeshift laboratory, as potential schools for the trial. A rapid appraisal will be conducted during the first week of the field-work and depending on the number of primary school children present in each village school, 10-15 children, aged 9-12 years, will be randomly selected and asked to provide 1 stool sample for parasitological examination with the Kato-Katz method (1 slide per sample). Only village schools with a prevalence of 70% or more in any of the common soil-transmitted helminths (STHs; *Ascaris lumbricoides, Trichuris trichiura* and hookworm) will be included for the recruitment process of the trial.

**1.2 Recruitment, baseline, intervention and follow-ups**

*Recruitment* - Given an estimated 70% prevalence and 50% loss to follow-up, **250** children have to be recruited to achieve a power of 80% at an alpha error of 5% to detect statistically significant differences in the physical fitness (difference of 2.5 mL/kg/min is considered to be of clinical relevance) and strength values between the albendazole and placebo groups. In each village, the village doctor, chief and teachers will be briefed on the aims of the study. All primary school children, aged 9-12 years will be gathered and the teachers will explain the study to the children and encourage them to participate in it, highlighting the physical fitness and strength tests at the end of the parasitological examination. Written informed consent will be signed by the childrens’ parents/guardians on their behalf.

*Baseline* - Once informed consent has been obtained, the 1st labeled (name, ID number) stool container will be distributed and collected the next day. During the collection of the 1st stool container, the 2nd labeled stool container will be given out and collected the day after. Only children who have submitted 2 stool samples and are infected with one or more of the common STHs will be included in further tests and follow-ups. All infected children are subjected to anthropometric measurements, hemoglobin measurements, 20 m shuttle run test, grip strength test and standing broad jump test.

*Intervention* – Only infected children who have completed all the baseline assessments will be randomly allocated to the two treatment arms:

Treatment arm 1: triple-dose albendazole (400 mg daily for 3 consecutive days)

Treatment arm 2: triple-dose placebo (daily for 3 consecutive days)

Each dose of treatment will be provided in person everyday for 3 consecutive days. During the administration of the treatments, children will have to swallow the tablets on the spot and in front of a field member. Water will be provided.

*Follow-ups* – The 1st, 2nd and 3rd follow-ups will be performed in December 2011, March and June 2012 respectively. In the 1st follow-up, only the parasitological examination, hemoglobin measurements, 20 m shuttle run test, grip strength test and standing broad jump test will be carried out. While in the 2nd and 3rd follow-ups, all the examination and tests as performed at baseline will be repeated.

*End of trial* – All participants will be offered a free single dose of 400 mg albendazole.

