**2.2 Participants exclusion criteria:**

1. Children below the age of 9 years or above 12 years
2. No written informed consent
3. Less than 2 stool samples submitted at baseline
4. Presence of medical condition that prevents child from completing the physical fitness and strength tests or refusal of child to do the tests.
5. No infection with any soil-transmitted helminth.
6. Presence of systemic illness, as assessed by a medical doctor at baseline,
7. Known or reported drug allergy to albendazole
8. Attending other clinical trials during the study period
9. Received anthelminthics in the previous 6 months

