**3.6 Standing broad jump test**

Before the start of the test, the field worker will demonstrate how to do the standing broad jump. Each child will then stand behind a straight line and jump as far forward as possible with both legs. He/she will have **2 tries** (with a 15-seconds rest in between) and the **longest jump** will be recorded (to the nearest 0.1 cm). The distance of the jump will be measured from the starting line to the heel of the most back foot.

For components 2.2-2.6, **3 stations will be set up, each attended by 2-3 field workers**. The 1st station will consist of the anthropometric and hemoglobin measurements. The 2nd station will consist of the grip strength and standing broad jump tests and the 3rd station will consist of the 20 m shuttle run test. Each child will hold on to a record sheet and as they move from one station to the other, the results of the various measurements and tests will be recorded on it. Once he/she has completed all the stations, the record sheet will be collected. During all the physical fitness and strength tests, the village doctor will be present to ensure that medical attention could be given immediately if required. All measurements and tests will take place from 9am-12pm in the morning and 2-5pm in the afternoon. The order and timing at which the different village schools will be approached will be kept approximately the same at baseline and the subsequent follow-ups. **Air temperature and humidity** of the testing areas will also be monitored.

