| 31.10 | | Anthropometric measurements, physical fitness tests and hemoglobin measurement (Baseline for 三队); (开始测体能，血红蛋白，身高体重) |
| 1.11 | | Anthropometric measurements, physical fitness tests and hemoglobin measurement (Baseline for 老寨，空坎2队). |
| 2.11 | | Anthropometric measurements, physical fitness tests and hemoglobin measurement (Baseline for 四队，新囡). |
| 3.11 | | Anthropometric measurements, physical fitness tests and hemoglobin measurement (Baseline for 空坎1队). |
| 4.11 | | Anthropometric measurements, physical fitness tests and hemoglobin measurement (Baseline for 曼别，曼纳). |
| 5.11- 6.11 | | Break from weekend 周末度假 |
| 7.11 | | Start of intervention (发药)for all villages (1st dose) 第一次发药。 |
| 8.11 | | 2nd dose for all villages第二次发药。 |
| 9.11 | | 3rd dose for all villages第三次发药 |
| 10.11-11.11 | | Extra days for intervention if needed. (发药) |
| 12.11-14.11 | | Testing of nutritional assessment methods in Upper Nanwen village (3-5 families). 南温上寨营养观测。 |
| 15.11-27.11 | | Break from fieldwork; Data entry. |
| **Dec 2011十二月** | |  |
| 28.11 | | 1st follow up starts; Distribution of 1st stool containers for 三队，老寨 during school hours (Estimated 102 students aged 9-12 years). （粪样检测）开始第一次随访，发粪盒给三队和老寨的在校学生（估计102个9～12的学生）。 |
| 29.11 | | Collection of 1st stool samples; Distribution of 2nd stool containers for 三队，老寨 during school hours; Parasitological examination (2 Kato-Katz slides and 1 Baermann per sample). 收第一次粪样，收到第一次粪样者同时发给第二次粪盒。寄生虫学检查同上。 |
| 30.11 | | Collection of 2nd stool samples; Parasitological examination; Distribution of 1st stool containers for 四队，新囡 during school hours (Estimated 45 students aged 9-12 years).收集第二次粪样。给四队和新囡的在校学生发第一次粪盒（估计有45个9～12岁的学生）。 |
| 1.12 | | Collection of 1st stool samples; Distribution of 2nd stool containers for 四队，新囡 during school hours; Parasitological examination. 收第一次粪样，收到第一次粪样者同时发给第二次粪盒。寄生虫学检查同上。 |
| 2.12 | | Collection of 2nd stool samples; Parasitological examination. |
| 3.12-4.12 | | Break from weekend. |
| 5.12 | | Distribution of 1st stool containers for 空坎1队， 空坎2队 during school hours (Estimated 59 students aged 9-12 years). 收集第二次粪样。给空坎1队和空坎2队的在校学生发第一次粪盒（估计有59个9～12岁的学生）； |
| 6.12 | | Collection of 1st stool samples; Distribution of 2nd stool containers for 空坎1队， 空坎2队 during school hours; Parasitological examination. 收第一次粪样，收到第一次粪样者同时发给第二次粪盒。寄生虫学检查同上。 |

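### In the text shown, no step asks about or records symptoms after albendazole or placebo, so the planned data allow no comparison of symptoms or reactions between the arms

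*Protocol*

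**What the plan says.** **Dosing.** Section 1.2 gives each child three daily doses in person: "During the administration of the treatments, children will have to swallow the tablets on the spot and in front of a field member". Water is provided. No other step is described for the dosing days, which the Section 5 timeline puts on 7, 8 and 9 November.

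**Follow-ups.** For December, Section 1.2 lists "In the 1st follow-up, only the parasitological examination, hemoglobin measurements, 20 m shuttle run test, grip strength test and standing broad jump test". For March and June, "all the examination and tests as performed at baseline will be repeated".

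**Records and medical cover.** Section 3.6 describes a sheet that the child carries between test stations, and "the results of the various measurements and tests will be recorded on it". During the fitness and strength tests, "the village doctor will be present to ensure that medical attention could be given immediately if required". The text shown does not say the same for dosing.

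**Allergy.** Section 2.2 excludes children with "Known or reported drug allergy to albendazole".

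**After dosing.** The timeline gives 10-11 November as "Extra days for intervention if needed". On 12-14 November it has nutrition-method testing in Upper Nanwen, which is not among the eight villages listed for the trial. The entry for 15-27 November is "Break from fieldwork; Data entry".

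**Analysis.** Section 4 compares anthropometry, fitness scores and haemoglobin between the groups and assesses infection intensity, cure and re-infection. It names no symptom or reaction outcome.

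**The concern.** Children aged 9 to 12 receive a drug or a placebo on three consecutive days. The allergy criterion screens out only a reaction already known or reported. A first reaction, after dose 1, would reach the trial team only if it were obvious or the child volunteered it.

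The second loss is information. Randomisation, a similar-looking placebo and blinded field staff are already in place, and these are what is needed to separate complaints caused by the tablets from background illness. If no answers are collected by child number, that design cannot be used for symptoms. This is not a detail that an analysis plan can settle later, because asking and recording is field work.

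**Working it through.** The main check is a reading of every procedure, record and outcome in the text shown.

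| Place in the Protocol | What is done | Symptoms asked about and recorded? |
|---|---|---|
| 1.2 Intervention; timeline 7-9 November | observed swallow, water | not described |
| 1.2 Follow-ups | stool examination, haemoglobin, fitness and strength tests; anthropometry in March and June | not described |
| 3.4 Shuttle run | children are told to voice discomfort beforehand | prompted, but only to decide who runs; no record specified |
| 3.6 Stations | record sheet; village doctor present at the tests | sheet holds measurement and test results |
| 4 Analysis | comparison of measured outcomes | no symptom outcome |

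The shuttle-run prompt is the nearest thing to a symptom question. At the 1st follow-up it falls on 12-16 December, which is 33 to 37 days after 9 November.

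**Gap after dose 3.** Dates and pupil numbers are from the timeline. The first contact is the handing out of stool containers.

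| Village pair | Pupils listed | First contact | Days from 9 November |
|---|---|---|---|
| 1 | 102 | 28 November | 19 |
| 2 | 45 | 30 November | 21 |
| 3 | 59 | 5 December | 26 |
| 4 | 68 | 7 December | 28 |

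Weighted mean: (102×19 + 45×21 + 59×26 + 68×28)/274 = 6321/274 = 23.1 days. The weights are all pupils listed, since the number randomised per village is not known. From 12 to 27 November, 16 days, no contact with trial children is planned.

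**Number of children concerned.** The Protocol does not state the number randomised, so a range is needed.
- 250 × 0.70 × 0.80 = 140, if 70% of recruits are infected and 80% of those finish baseline (the 80% is an assumption).
- 250 × 0.70 = 175, if all infected recruits finish.
- 250, if every pack is used (upper limit).

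That is about 70, 87 or 125 per arm, and 420, 525 or 750 doses. Checks before doses 2 and 3 would number 2 × 140 = 280 to 2 × 250 = 500.

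**What recording could show.** The event rates here are assumptions and do not come from the Protocol.

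| Per arm | Upper 95% one-sided bound if no events, 1 − 0.05^(1/n) | Chance of at least one event at 1 in 50, 1 − 0.98^n | 95% half-width for the arm difference at 10% in each arm, 1.96 × √(2 × 0.1 × 0.9/n) |
|---|---|---|---|
| 70 | 4.2% | 76% | 9.9 points |
| 87 | 3.4% | 83% | 8.9 points |
| 125 | 2.4% | 92% | 7.4 points |

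The figures apply to whatever the questions capture, which under the fix below is events after doses 1 and 2.

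**The case against.** **This is an omission, and some pages are not visible.** The design figure, the consent pages and the record forms mentioned in the timeline are not shown, and any of them could hold a procedure. This stands as a limit: the point covers the text shown and does not establish that nothing was collected. But the numbered sections run unbroken from 1 to 5, and those that describe dosing, field procedures, analysis and timeline contain no such step.

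**Harm can be compared through the measured outcomes.** A reader might infer that the trial can make no harms comparison at all. The Protocol does not support that. Haemoglobin and fitness are measured at every follow-up and anthropometry at the last two, and all are compared by arm. A deterioration in them on albendazole would be visible. What is missing is a comparison of symptoms and reactions.

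**Children are seen on every dosing day.** A reader might also infer that children are re-dosed with no check whatever. That is firmer than the text allows: a field member meets each child on days 2 and 3 and may notice or be told of a reaction. What the text lacks is a question put to every child and a record of the answer.

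**The word limiting the December list.** It could be read as ruling out symptom questions. Its evident purpose is to mark that anthropometry is skipped at that visit, so nothing here rests on it.

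**The yield is small.** The arm comparison would be known only to about 7 to 10 percentage points at an assumed 10% rate. This stands, and it keeps the point modest. The case rests more on the children's safety between doses and on the low cost.

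**Conclusion.** The point holds in a limited form. In the text shown, no step asks about or records symptoms after either treatment. The next planned contact after the scheduled third dose is 19 to 28 days later, and the shuttle-run prompt does not fill the gap. The planned data therefore allow no comparison of symptoms or reactions with placebo.

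The size is 140 to 250 children and 420 to 750 doses. The lower end assumes 70% infected and 80% completing baseline. The gap follows from the timeline alone, counted from 9 November; it would be up to two days shorter for a child dosed on the spare days. The yield figures rest on assumed event rates and show only an order of magnitude.

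The efficacy comparison is not touched. The sponsor should make the change, but the point does not undermine the trial's main question. If a form outside the text shown already does this, a sentence in Section 1.2 citing it would be enough.

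**What to change.** Add to the Intervention paragraph of Section 1.2: *Before dose 2 and before dose 3 the blinded field member asks a short fixed set of symptom questions and records the answers by child number. A child with a suspected allergic reaction is not re-dosed until seen by the village doctor.* Report the number of children with at least one event, by arm.

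**Cost.**
- A few minutes per child at two contacts that already exist. At an assumed 3 minutes, 140 to 250 children need 7 to 12.5 staff-hours per check day, on days when all villages are dosed.
- Prompted questions will bring up background complaints in both arms. The placebo arm is there to separate these.
- Rarely, a dose will be delayed or missed, possibly more often in one arm. The spare days of 10-11 November can absorb a short delay, but the three doses are then no longer consecutive.

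**Not included.** A recall question at the 1st follow-up would ask about dose 3 after 19 to 28 days and give weak answers, so events after dose 3 remain largely uncaptured. A rule to hold doses for any more-than-mild symptom is also left out, because it would alter the three-consecutive-day regimen more often and is a matter of clinical judgement.

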**1.3 Randomization and blinding procedures**

Block randomization will be carried out to ensure that both treatment arms have roughly equal sample sizes. [name] will hold the code to the randomization. In the field, class lists from the schools will be obtained and following the order of the list, each child will be assigned a random number from a list of 250 random numbers generated from R [“sample (1:250, 250)”]. This random number will be the number on the packed treatment to be given to the child.

This trial will be double blinded. The albendazole and placebo tablets will look similar and the children will not be told about the presence of the placebo tablets. All investigators in the field will also be blinded to the treatment status of the children, since [name] will carry out the packing of the tablets in Basel. For each child, the three doses of tablets (albendazole or placebo) will be wrapped with a piece of aluminium foil and sealed in a small Ziploc bag and labeled with a number (from 1-250).

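### Section 1.3 states block randomisation but hands out packs by an unrestricted permutation of 1–250, so blocks built on pack numbers would have no effect

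*Protocol*

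**What the plan says.** Section 1.3 opens with the method and its single stated purpose: "Block randomization will be carried out to ensure that both treatment arms have roughly equal sample sizes". It gives no block size and names no stratification factor.

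The same paragraph then describes the field step. Field staff work down the class lists of the schools, and "each child will be assigned a random number from a list of 250 random numbers generated from R"; the R call shown is a single permutation of the integers 1 to 250. The link to treatment is explicit: "This random number will be the number on the packed treatment to be given to the child". Packs are made up beforehand in Basel, each "sealed in a small Ziploc bag and labeled with a number (from 1-250").

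Section 1.2 limits who is allocated: "Only infected children who have completed all the baseline assessments will be randomly allocated to the two treatment arms". It also gives the planning figures: "Given an estimated 70% prevalence and 50% loss to follow-up, 250 children have to be recruited".

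The timeline in section 5 lists eight villages in four pairs, with estimated numbers of children aged 9–12 for each pair.

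**The concern.** Permuted blocks balance the arms only if the units carrying the blocks are used up in block order. A list of treatments blocked on pack numbers loses that property once pack numbers are shuffled before hand-out, because the members of one block then go to children far apart on the class lists. Two statements in one paragraph therefore appear to describe different designs.

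Both sequences would give the same totals if all 250 packs were used. They will not be, since only infected children with complete baseline assessments are allocated, so the order of use matters.

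Two things are at stake. The trial could report a block-randomised design that it did not carry out. It could also give up, for nothing in return, balance within villages. Fitness, strength and haemoglobin are measured village by village over five days at baseline and again at the first follow-up, and section 3.6 has temperature and humidity monitored at the testing areas.

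**Working it through.** **Inputs.** 250 packs, 70% prevalence and 50% loss (sections 1.2 and 1.3); village-pair estimates of 102, 45, 59 and 68 children (section 5). Assumptions, because the protocol does not give them: 125 packs per arm; 70% infected in every village; each pair split evenly between its two villages; block sizes of 2 to 10.

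**The plan's own figure.** The protocol gives no figure for allocation balance. The recruitment target of 250 cannot be re-derived because no SD is stated, and this point does not depend on it.

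**Packs used.** 0.70 × 250 = 175. From the timeline, 102 + 45 + 59 + 68 = 274 and 0.70 × 274 = 191.8. So about 175–192 of 250 packs are used.

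**Overall arm size under the permutation.** The number in one arm among m packs drawn is hypergeometric, with SD = √[m × ¼ × (250 − m)/249].
- m = 175: √(43.75 × 75/249) = 3.63; 95% range 80–95; P(arm difference above 10) = 17%, above 20 = 0.6%.
- m = 192: √(48 × 58/249) = 3.34; 95% range 89–103; P(arm difference above 10) = 10%.
- m = 250: exactly 125:125.

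Efficiency of an 80/95 split relative to an even one: 4 × 80 × 95 / 175² = 0.993.

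**Balance along the sequence.** With blocks on pack numbers and permuted hand-out, about 50%, 38%, 32% and 25% of consecutive groups of 2, 4, 6 and 10 children are balanced. With intact blocks it is 100%.

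**By village pair** (71, 31, 41 and 48 infected children, 191 in all; 5,000 simulated lists per block size):

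| Packs used in | Mean arm difference per pair | Extreme | Overall difference |
|---|---|---|---|
| Block order | 1.0–1.7 | maximum 5 | 1 |
| Permuted order | 4.2–5.8 | 95th percentile 11–15 | mean about 5.4 |

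**By single village.** Size = half of the pair × 0.70 × 250/274, which gives 33, 33, 14, 14, 19, 19, 22 and 22 (176 in all). Under the permutation, the chance that a given village splits 2:1 or worse is 17% for n = 14 and 6% for n = 33. Over 40,000 permutations, at least one of the eight villages does so in about 64%, and two or more in about 26%. With blocks of 4 used in order, even without stratification, a village can start and finish mid-block, so its difference is at most 4. The worst case is 5:9 in a village of 14, which is not 2:1.

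**By test day.** The five baseline days hold 33, 52, 28, 19 and 44 children on these sizes. The chance that at least one day splits 2:1 or worse is 27%.

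**Precision cost of a village-adjusted comparison.** Expected efficiency relative to perfect within-village balance is 1 − Σ[(250 − n)/249]/Σn = 1 − (1,824/249)/176 = 0.96.

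**The case against.** The strongest reply is that the one stated aim, roughly equal arms, is met: drawing without replacement from 125 and 125 packs keeps the totals close, at under 1% efficiency loss. That stands.

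Several stronger readings are tempting and are not supported.
- *The permutation destroys the blocks.* The text does not say whether the blocks run along pack numbers or along the permuted list, and a code holder who knew the permutation could have built them along it. That reading rescues the blocks only if every position on the list is used. If ineligible children on the class list take up numbers, these blocks break as well.
- *A promised village balance is not delivered.* No stratification is stated, so none was promised.
- *Village and test day are the same thing.* Under the timeline, six of the eight villages share a test day with another, and section 3.6 keeps the order and timing of villages about the same at each visit.
- *The arm comparison is biased.* Children are allocated individually and at random, so uneven villages are ordinary chance error.
- *250 numbers cannot cover 274 listed children.* Under section 1.2 only eligible children are allocated, and about 175–192 fit within 250. What remains is that section 1.3 speaks of each child on the list and should say which children draw a number.

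The 64% figure also comes mainly from the smaller villages and depends on an even split of each pair, which the documents do not give. Adjustment for village may stand in an analysis plan that is not at hand.

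**Conclusion.** The point holds as an internal inconsistency in section 1.3, of minor to moderate severity. If the blocks follow pack numbers, the procedure described is a simple random draw without replacement, and calling it block randomisation is inaccurate. If they follow the permuted list, the text needs to say so and to keep ineligible children from using up positions.

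The consequence is limited. Overall arm sizes remain near equal and the comparison remains valid. The loss is balance along the allocation order and within villages, worth about 4% of precision in a village-adjusted comparison. These sizes rest on 125 packs per arm, 70% infection in every village and evenly split village pairs. The inconsistency itself rests on none of them.

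**What to change.** Reword section 1.3 so that it:
1. drops the `sample(1:250, 250)` step, or states that the blocks are built along the permuted list and that packs are used in that order;
2. lets only children confirmed eligible under section 1.2 draw a number;
3. reserves whole blocks for each village and gives the next unused pack to the next eligible child in class-list order;
4. records the block sizes in a document kept by the code holder and names village as the stratum.

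Within a village, blocks of 4 cap the arm difference at 2, and mixed blocks of 4 and 6 cap it at 3. Village should then enter the analysis model.

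The cost is a rewording, a village column on the pack list and a few unused packs. If packs are already numbered by block, no repacking is needed. The supply suffices: the timeline completes baseline testing before allocation starts, so eligible numbers are known. At most 3 packs per village go unused with blocks of 4 (192 + 8 × 3 = 216), or 5 if the last block is of 6 (192 + 8 × 5 = 232), both below 250.
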